### Schedule of assessments

The first study visit will be performed immediately after study participants provide written informed consent, enrolment and randomization. Anthropometric information, baseline treatment and laboratory data will be recorded. Elective cardiac surgery will be programmed within 30 days of the first visit. The research team will provide study medication to each participant. Doses 1–5 of study medication will be administered daily on the last 5 days before surgery (Days –5 to –1). The sixth dose will be administered within the first 8 h after surgery (Day 0). Doses 7–13 will be administered daily during the first 7 days after surgery (Fig. 1). Previous research has not adequately defined the best timing for SGLT2i initiation to prevent ischemia–reperfusion injury with protocols starting SGLT2i administration both before and after the onset of injury [21, 23, 24]. However, empagliflozin has been shown to reach the peak of its glycosuric effect within the first 24 h after its administration, with further stabilization over the next 72 h. Moreover, renal protective effects of SGLT2i seem to appear early after treatment initiation [23, 37]. We chose to start study medication 5 days before surgery to ensure a stable and sustained effect of empagliflozin on the kidney.

The visit schedule is summarized in Fig. 2. Vital signs, blood and urine samples, as well as information about study endpoints, adverse events and other outcomes of interest, will be recorded in each visit.

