### Outcome definitions and background medication

The primary endpoint of the study will be the time to the first occurrence of any major adverse kidney event during the first 90 days after surgery (MAKE90). The components of MAKE90 will be a ≥25% eGFR decline from preoperative baseline, the start of renal replacement therapy or patient death. Secondary, tertiary and safety endpoints are listed in Table 2. Treating physicians will be responsible for adjudicating possible postoperative complications.

**Table 2: tbl2:** Primary, secondary, tertiary and safety endpoint of the VERTIGO trial.

Primary endpoint
Proportion of patients that present MAKE90, defined as one or more of the following:
- ≥25% eGFR decline from preoperative baseline
- Start of renal replacement therapy
- Patient death
Secondary endpoints
- Proportion of participants who developed any stage of AKI defined according to KDIGO guidelines during index admission
- Proportion of patients who suffered a Stage 3 AKI according to KDIGO guidelines during index admission
- Proportion of patients who required renal replacement therapy during index admission
- Proportion of patients who died during index admission
- Proportion of patients that maintain ≥25% eGFR decline from preoperative baseline 90 days after surgery
Tertiary endpoints
- Difference in total time (h) on mechanical ventilation
- Difference in mean daily dose of inotropes used
- Difference in plasma levels of interleukin-6 and C-reactive protein
- Difference in urinary levels of interleukin-18 and protein/creatinine ratio
- Difference in serum interleukin-1β and interleukin-18 concentration
- Time to first occurrence of postoperative complications, defined as low cardiac output, reoperation for bleeding, delirium, seizures, surgical site infection, sepsis, arrhythmias, cardiac arrest, pneumonia, liver dysfunction or need for blood transfusion
- Difference in total time (days) spent in the ICU
- Difference in total time (days) of index hospital stay
- Difference in rates of hospital readmission due to cardiovascular disease
- Difference in frailty evaluation, represented by the results of the Clinical Frailty Scale
- Patient reported quality of life EuroQoL-5D
Safety endpoints
- Adverse events
- Serious adverse events (i.e. adverse event that results in death, is considered life-threatening, requires or extends an hospitalization episode, causes disability or is judged as such according to the clinical criteria of the research team)

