Primary endpoint analysis will be based on the intention-to-treat population, defined as all validly randomized patients. In the analysis of the primary endpoint, study treatments will be compared using a Cox proportional hazards regression model with a factor for the treatment group. Hazard ratio, 95% confidence interval and *P*-value will be reported. Kaplan–Meier estimates of the cumulative incidence to the occurrence of MAKE90 will be calculated. Secondary endpoints will be tested in a similar manner. If superiority is achieved for the primary endpoint, the secondary endpoints will be tested following a hierarchical order, as follows. (i) Any stage of AKI defined according to Kidney Disease: Improving Global Outcomes (KDIGO) guidelines during index admission. (ii) Stage 3 AKI according to KDIGO guidelines during index admission. (iii) Time to renal replacement therapy initiation during index admission. (iv) Time to death from any cause. Statistical significance will be required before testing the next hypothesis in the hierarchy. The effects of the planned intervention on primary and secondary outcomes will also be assessed in subanalyses stratified by sex, baseline eGFR, diabetic status and type of planned surgery (valvular/coronary/valvular and coronary).

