Secondary endpoints will provide additional information on the effect of empagliflozin on the incidence of AKI immediately after cardiac surgery. The use of KDIGO consensus criteria for AKI, a classification that employs serum creatinine levels as well as urine output to classify AKI severity [48], will allow for easier comparison of efficacy across different therapeutic strategies. The description of the effect of the planned intervention on kidney function will be completed with urinary biomarkers of AKI such as interleukin-18 or DKK3/albumin ratio. The results of secondary endpoints, in combination with the primary endpoint of the study, will provide an extensive exploration of the efficacy of empagliflozin in preventing CSA-AKI in the study sample using clinically meaningful outcomes.

Tertiary endpoints, such as time on mechanical ventilation after surgery, average inotrope dose, biomarkers of inflammation and AKI, frailty assessment, incidence of postoperative complications, as well as total length of intensive care unit and hospital stay, or need for hospital readmission for cardiovascular disease, will allow us to analyze the short- and medium-term postoperative recovery of patients.

The study will also provide information on the safety of perioperative empagliflozin in patients that require elective cardiac surgery. The safety profile of SGLT2i, and specifically empagliflozin, has been extensively described in recent years, both in patients with diabetes as well as in non-diabetic chronic kidney disease [25, 49, 50]. Empagliflozin is generally well tolerated, and specific potential complications, such as symptomatic dehydration, hypoglycemia or urinary tract infections, will be carefully monitored and reported throughout the trial.

Although multiple interventions have been tested aiming to reduce the incidence and severity of CSA-AKI, no treatment strategy has been successfully translated into daily clinical practice. Therefore, our study will be placebo controlled. All participants in the study will receive standard treatment as per treating physicians and local practice guidelines. Randomization will be stratified by center and diabetic status. To minimize the risk of selection bias, block randomization with random block sizes will be employed.

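### The first two hierarchical secondary endpoints count urine output, which a glycosuric study drug may shift in one arm; a parallel creatinine-based AKI analysis should be prespecified

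*Protocol article*

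**What the plan says.** Four parts of the protocol article bear on this point.

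- **Endpoints.** Table 2 (Outcome definitions and background medication) lists as the first secondary endpoint: "Proportion of participants who developed any stage of AKI defined according to KDIGO guidelines during index admission". The Stage 3 endpoint follows it. Neither is restricted to creatinine.
- **Hierarchy.** Sample size calculation and statistical analyses states that, once the primary endpoint shows superiority, "the secondary endpoints will be tested following a hierarchical order". Step (i) is "Any stage of AKI defined according to Kidney Disease: Improving Global Outcomes (KDIGO) guidelines during index admission" and step (ii) is "Stage 3 AKI according to KDIGO guidelines during index admission". Steps (iii) and (iv) are renal replacement therapy and death, and each step must be significant before the next is tested.
- **Definition.** The Discussion describes the choice as follows: "The use of KDIGO consensus criteria for AKI, a classification that employs serum creatinine levels as well as urine output to classify AKI severity". The reason it gives for the choice is easier comparison between therapeutic strategies.
- **Drug exposure.** Schedule of assessments places doses on Days -5 to -1, within 8 hours after surgery, and daily for the first 7 postoperative days. In support of the early start it notes that "empagliflozin has been shown to reach the peak of its glycosuric effect within the first 24 h after its administration" and that the effect then stabilizes.

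The article does not mention that the drug's own action might affect the urine-output criterion.

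**The concern.** Glucose in the urine can be expected to carry water with it. A treated patient and a placebo patient with the same tubular injury may then differ in urine volume, and the treated patient would be less likely to fall below an oliguria threshold. In that case one limb of the AKI definition would reflect drug action as well as injury in one arm, and injury alone in the other. Randomization and blinding do not remove this, because it arises in the measurement.

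The interpretation of the AKI result is at stake. The Key Learning Points and the closing paragraph of the Discussion say that the trial will give evidence on the incidence and severity of AKI after cardiac surgery, and steps (i) and (ii) are the most immediate evidence for that. Without the two limbs shown separately, a reader could not tell diuresis from protection.

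**Working it through.** **1. The plan's own figure.** The article states no rate, effect size or power for the AKI endpoints. Its only sample size is for the primary endpoint: 25% versus 15%, one-sided 5%, 90% power. The two-proportion formula with pooled variance and no continuity correction gives 273 per group (546 in all). Then 273 / 0.90 = 303.3, rounded up to 304 per group (608 in all). Both stated totals are reproduced, and this point does not dispute them.

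**2. Overlap in time.** Dosing runs from Day -5 to Day 7. AKI is assessed over the index admission, and the Discussion refers to AKI immediately after surgery. The drug is therefore active by design in the period that matters for steps (i) and (ii).

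**3. Possible size of the urine-output distortion.** Inputs:
- AKI incidence p = 20% to 40% (Discussion).
- n = 304 per arm (all randomized patients).
- f = share of AKI cases identified by urine output alone, assumed 30% to 50%.
- m = share of those cases masked by diuresis, assumed 10% to 30%.
- No true effect on injury, and no drug effect on creatinine.

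The documents give neither f nor m. The distortion is p × f × m:
- Low: 0.20 × 0.30 × 0.10 = 0.006, so 20.0% versus 19.4%.
- High: 0.40 × 0.50 × 0.30 = 0.060, so 40.0% versus 34.0%.

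If the drug truly lowers AKI, the product applies to the lower rate in the treated arm, so for given f and m the distortion is smaller than these figures.

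**4. Rejection probability at step (i), ignoring the gate.** The normal approximation is Φ[(d − z·s0)/s1], where d is the difference and s0 and s1 are the pooled and unpooled standard errors.
- Low: (0.006 − 1.645 × 0.03226) / 0.03226 = −1.459, giving 7.2%.
- High: (0.060 − 1.645 × 0.03916) / 0.03908 = −0.113, giving 45.5%.

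On the favourable side of a two-sided 5% test (z = 1.960), the results are 3.8% and 33.4%. With 273 per arm, the one-sided results are 7.1% and 42.3%.

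These figures depend almost entirely on f and m. With 273 per arm, f from 20% to 60% and m from 25% to 50%, the distortion runs from 1 to 12 points and one-sided rejection from 9% to 91%.

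**5. Effect of the gate.** Step (i) is tested only after the primary endpoint succeeds, and eGFR decline, renal replacement therapy and death contain no urine-output criterion. If the drug has no effect on the primary endpoint, that gate opens falsely about 5% of the time (one-sided), so a false confirmatory step (i) cannot occur more often than that. If the two tests were independent, the rate would be 0.05 × 0.072 = 0.4% to 0.05 × 0.455 = 2.3%. Positive correlation would move it towards the 5% ceiling but not above it.

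**6. Direction.** The Introduction says that the class lowers intraglomerular pressure, and the Discussion lists symptomatic dehydration as a potential complication. Either could raise creatinine and push the other KDIGO limb against the drug. The sign of the net effect on full KDIGO cannot be settled from the article.

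**The case against.** A reader might infer that the plan carries a 7% to 46% chance of a false AKI claim. The documents do not support that. Those percentages describe an ungated test under unsourced inputs, and the gate on the primary endpoint caps the confirmatory error as shown above. A reader might also infer that a spurious step (i) passes its error down the hierarchy. It would open the later steps, but steps (iii) and (iv) have no urine-output limb and must reach significance on their own data.

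Further objections have weight:
- The article states glycosuria but never says that urine volume rises.
- Dehydration is named as a potential complication and not as an expected effect.
- KDIGO is a consensus definition, chosen for a stated reason. Replacing it with creatinine alone would discard 30% to 50% of cases on the assumption used above, and would keep any drug effect on creatinine.
- AKI is not the only evidence on kidney injury. Table 2 also has renal replacement therapy and sustained eGFR decline at 90 days, and the Discussion adds urinary biomarkers.
- Stage 3 is probably less exposed, since those cases may also qualify through creatinine or renal replacement therapy.

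Operational AKI rules may also sit in the full protocol or analysis plan, which is not shown. These objections limit the claim and argue against replacing the endpoint. They do not remove the central point: the article chooses a definition with a urine-output limb for a glycosuric drug and does not address how the result will be interpreted.

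**Conclusion.** The point holds as a question of interpretation at steps (i) and (ii). One limb of the AKI definition can be shifted by the study drug in one arm without kidney protection. Under the stated assumptions the shift is 0.6 to 6.0 percentage points in any-stage AKI, and smaller for given f and m if the drug truly lowers AKI. No figure can be given for Stage 3, where the effect should be smaller. The conclusion rests on the inference that glycosuria raises urine volume, and on values of f and m that the documents do not supply.

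The urine-output problem does not reach the primary endpoint. If the primary endpoint succeeds, the risk is that an AKI effect is exaggerated or wrongly attributed to protection. Because creatinine may move the other way, the documents do not establish a net bias in favour of empagliflozin. That uncertainty is itself a reason to show the two limbs separately.

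**What to change.** Keep full KDIGO at steps (i) and (ii), and make three additions before unblinding:

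1. In Sample size calculation and statistical analyses, prespecify the same two analyses with AKI and Stage 3 AKI defined by the KDIGO serum-creatinine criteria plus renal replacement therapy.
2. Report by arm the number of AKI cases that met the urine-output criterion only.
3. In the Discussion, including its closing summary, state that prevention of AKI after cardiac surgery will be concluded only if the creatinine-based result is consistent with the full-KDIGO result.

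The cost is a little extra analysis and a more cautious AKI claim if the two definitions disagree. Comparability with other trials, the article's stated reason for using KDIGO, is preserved. Dosing, clinical management, the primary endpoint and the sample size do not change.

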## Data Availability

No new data were generated or analysed in support of this research.
